## Discussion

Chemotherapy-induced peripheral neuropathy is a common adverse reaction related to chemotherapeutic drugs. Approximately 50–90% of patients who receive chemotherapy will have CIPN, and 30–40% of them will develop chronic adverse reactions (33–35). For example, among patients with breast cancer receiving docetaxel treatment, 42% still had CIPN symptoms for 2 years after treatment; 2 years after oxaliplatin treatment, the incidence of CIPN in patients with colorectal cancer was 84% (36, 37). CIPN is mainly manifested as symmetrical numbness, pain, and paresthesia at the ends of the extremities. In severe cases, it may involve the proximal extremities and be accompanied by the disappearance of tendon reflex or dyskinesia. The pathogenesis of CIPN is still not clear, which may be related to the damage of sensory neurons in the dorsal root ganglion (DRG), abnormal secretion of pro-inflammatory cytokines, mitochondrial dysfunction and oxidative stress, the abnormal immune system triggered by chemotherapy, microvascular destruction and axonal degeneration, imbalance of ion channels, and others factors (3, 38–40). At present, CIPN has no specific therapeutic drug, and duloxetine is the only drug recommended in the clinical guidelines (41), but it is not widely used in clinical practice because of its side effects. Due to its high prevalence and difficulty to cure, CIPN constitutes a significant clinical problem for patients with cancer as well as their healthcare providers.

Utidelone is a new chemotherapeutic drug in recent years, which is mainly used to treat recurrent or metastatic breast cancer (9), especially in patients who need high-dose anthracycline and taxus drugs or who develop resistance to them (10, 11). However, the main side effect of UTD1 can be more severe PN symptoms. It can cause patients severe numbness in their hands and feet, sore limbs and pain, and even render them unable to walk. Severe PN caused by UTD1 may lead to the reduction or withdrawal of chemotherapeutic drugs and affect clinical efficacy. However, at present, there are very seldom prevention and treatment schemes. Although the pathogenesis of PN caused by UTD1 is not clear, its symptoms are similar to those caused by other chemotherapeutic drugs. Considering that EA therapy has a good treatment effect on PN caused by these kinds of chemotherapeutic drugs (19), we speculate that EA can also improve the symptoms of PN caused by UTD1 and alleviate the numbness and pain symptoms in the patient's hands and feet. Therefore, we designed a study protocol of a randomized controlled trial by using EA technology as the main treatment method and oral drugs as the control to treat PN caused by UTD1. The EA therapy will be used to treat PN caused by UTD1 for the first time. The results of this trial will help us determine whether EA can treat PN caused by UTD1 and improve the quality of life of patients with advanced breast cancer.

At present, there are no definite tools for evaluating the PN caused by UTD1. A numeric rating scale (NRS) for cancer pain has been applied to the clinical evaluation of various pain degrees since 1950 (42). The number between 0 and 10 is used to represent the pain intensity, which is applicable to the elderly and those with low educational levels person (43). However, due to its low sensitivity, it is rarely used to evaluate the degree of CIPN. The evaluation scale of EORTC QLQ-CIPN20 is a patient-self-reported questionnaire (26). As doctors and patients have different understandings of the disease, different evaluation results of CIPN may result. Especially when it comes to sensory disorders, there are significant differences between the two groups. Therefore, a reliable assessment of the severity of CIPN-related sensory disorders should combine clinical symptoms with a professional assessment. Peripheral NCV is commonly used to evaluate the degree of peripheral nerve damage. However, as our study subjects are patients with advanced breast cancer, NCV tests may cause discomfort to patients or increase their psychological burden. Therefore, we may recommend this test to patients who are willing, but it will not be used as the outcome of our study. In this study, the severity of PN caused by UTD1 will be evaluated using the evaluation scale of peripheral neurotoxicity of chemotherapeutic drugs according to EORTC QLQ-CIPN20 as the main outcome. To evaluate the accuracy, the professional evaluator will also comprehensively evaluate the peripheral neurotoxicity severity of the patient according to the patient's clinical symptoms and physical examination of the peripheral nervous system, and the severity grade will be determined according to NCCN5.0. In addition, the patient's quality of life will be evaluated according to EORTC QLQ-C30, and AEs during the study will be recorded, which will make the study results more convincing.

Although duloxetine is the only drug recommended by the guidelines to treat CIPN, it is rarely used in clinical practice due to the acceptance of antidepressants, adverse reactions of the central nervous system and digestive system, and its limited efficacy (duloxetine 58% vs. placebo 38%) (44). Neurotrophic drugs are widely used in the clinical treatment of peripheral nerve diseases and MeCbl is the most commonly used. Some studies showed that MeCbl can improve the numbness of hands and feet caused by all kinds of PN (45, 46) and is considered a safe, effective, and generally well-tolerated drug for treating PN (47). In clinical treatment, MeCbl is most widely used in the treatment of CIPN symptoms, which is also based on our clinical data. When reviewing the previous treatment data, it was found that seldom few patients were willing to receive drug treatment such as duloxetine, and pregabalin was used more for patients with neuralgia. Therefore, we chose MeCbl as the control drug to treat PN caused by UTD1 according to previous clinical experience. From another perspective, this study will also clarify the effectiveness and safety of MeCbl in the treatment of PN caused by UTD1.

Utidelone is mainly used for patients with recurrent or metastatic advanced breast cancer. These patients mainly have accumulated neurotoxicity of chemotherapeutic drugs in their bodies because they previously used large doses of anthracycline and taxus drugs. UTD1 may induce neurotoxicity accumulated by other chemotherapeutic drugs, or it may itself be a pathogenic drug that causes severe PN symptoms, but in either case, the patients who developed PN symptoms are related to UTD1, thus our research theme is consistent. The severity of PN symptoms caused by UTD1 is closely related to drug dose accumulation. The PN symptoms of patients who used UTD1 in the first few times are usually not serious, and these patients' symptoms can be relieved during the interval of chemotherapy, so they usually do not want other interventions. However, with the increase in chemotherapy times, the PN symptoms of patients become more serious. Their symptoms cannot be relieved during the chemotherapy interval, and they feel numbness and discomfort at the end of the limbs all the time. PN caused by UTD1 is mainly characterized by numbness, tingling, or other abnormal feelings in the hands and feet. Generally, the first symptom that patients experience is sensory nerve damage. However, patients who have used chemotherapy for UTD1 often develop motor nerve function damage. In particular, patients have weakness in both lower limbs and difficulty walking, some patients may also have muscle atrophy, but autonomic nerve function is rarely affected. It is highlighted here that sensory nerve symptoms are the most common in patients. Therefore, patients with only sensory nerve symptoms, such as patients with a certain degree of numbness, will be included in this study. During the recruitment, the doctors will evaluate the symptoms of PN according to the patient's condition. For the patient's simple numbness of individual fingers, perhaps the symptom of nerve compression, we will identify it clinically.

This study will clarify the efficacy of EA in the treatment of PN caused by UTD1 and provide technical guidance for clinical treatment. The results will further provide new clues, new ideas, and new methods for acupuncture in the treatment of nervous system diseases and cancer-related diseases. Finally, we hope the results of this study will effectively improve the PN symptoms caused by UTD1 in patients with advanced breast cancer, reduce their pain, and improve their quality of life.

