### Study procedure

The duration of the trial will include three study phases, including screening in the baseline phase (week 0), 4-week treatment phase (weeks 1–4), and follow-up phase (week 8). The qualification of prospective participants will be determined by researchers who will not be involved in the assessment or treatment. At the screening meeting, patients will be given more detailed information about the study procedures. Before the first treatment (baseline, week 0), after the last treatment (post-treatment, week 4), and in the fourth week of follow-up after treatment (week 8), all participants will be required to complete several questionnaires as the outcomes of the study to evaluate the curative effect, including EORTC QLQ-CIPN20 and EORTC QLQ-C30 questionnaires. The participants cannot take drugs that may influence the outcomes of the study during the trial, including pain drugs or unspecified CIPN-related therapeutic drugs. If the patient has to take drugs that will influence the outcomes of the study due to disease progression, the patient will be considered to have dropped out. To promote enrollment, all treatment costs and outcome measurements will be free for participants.

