### Inclusion criteria and exclusion criteria

All participants will be screened according to the inclusion criteria and exclusion criteria at the baseline (Table 2 for details).

**Table 2 T2:** Inclusion criteria and exclusion criteria.

**Patients who meet the following requirements will be considered for inclusion:**	**Patients will be excluded if they have:**
(1) Diagnosed as advanced breast cancer and PN symptoms occur after using UTD1. The patient had no obvious PN symptoms before using UTD1; (2) Over 18 and under 70 years old, and the expected survival time was ≥6 months; (3) Have daily living ability and can complete all questionnaire investigation; (4) No serious heart, brain, kidney, and other diseases, KPS score >70; (5) Clear consciousness without severe mental illness or cognitive impairment; (6) Sign the written informed consent form.	(1) Diagnoses as other severe systemic diseases (e.g., cardiovascular disease, acute infectious disease, hematopathy, et al.); (2) Diagnoses as severe mental disorders, like schizophrenia; (3) PN caused by other diseases, such as diabetic peripheral neuropathy; (4) Alcohol and/or other drug abuse or dependence; (5) Pregnant and lactating women; (6) Participating in other clinical trials.

PN, peripheral neuropathy; UTD1, Utidelone; KPS, Karnofsky performance status.

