### Randomization and allocation concealment

The randomization will be performed by the Department of Scientific Research, Zhejiang Cancer Hospital. A randomization method will be used to generate the random allocation sequence of two groups in a ratio of 1:1; two groups of random serial numbers will be randomly placed in opaque, sealed envelopes by other staff who will not be involved in the study to ensure the concealment of distribution. These envelopes will be printed with consecutive numbers on the outside. The envelope with the corresponding serial number will be selected according to the participant's visit order.

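### UTD1 status (continuing or stopped) is not used at entry, allocation or analysis, although the protocol ties neuropathy severity to UTD1 accumulation; the cost is precision and interpretability, not systematic bias

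*Protocol article*

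**What the plan says.** All references are to the protocol article.

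- **Discussion, on the course of the neuropathy.** "The severity of PN symptoms caused by UTD1 is closely related to drug dose accumulation". It adds that "with the increase in chemotherapy times, the PN symptoms of patients become more serious". For the first few uses only, it says that "these patients' symptoms can be relieved during the interval of chemotherapy".
- **Discussion, on the consequence for chemotherapy.** "Severe PN caused by UTD1 may lead to the reduction or withdrawal of chemotherapeutic drugs and affect clinical efficacy". The Background makes the same point, also with the word may.
- **Inclusion and exclusion criteria (Table 2).** The criterion that concerns UTD1 reads "Diagnosed as advanced breast cancer and PN symptoms occur after using UTD1", with no obvious neuropathy beforehand. Neither list mentions ongoing, stopped or planned UTD1, number of courses, cumulative dose or time since the last dose.
- **Randomization and allocation concealment.** "A randomization method will be used to generate the random allocation sequence of two groups in a ratio of 1:1". Numbered envelopes are taken in visit order. No stratification factor is named.
- **Study procedure.** Drugs that may affect the outcomes are barred, "including pain drugs or unspecified CIPN-related therapeutic drugs". UTD1 is not mentioned, so this rule does not settle whether participants are on or off it.
- **Schedule (Table 1).** Assessments fall at weeks 0, 4 and 8. No UTD1 exposure item is listed.
- **Statistical analysis.** Two independent samples are compared by t-test or a non-parametric test, two-sided at 0.05. No covariate is named.
- **Blinding.** Participants and acupuncturists are not blinded.

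**The concern.** The protocol names UTD1 accumulation as closely related to the severity that its primary outcomes measure. It then neither conditions on UTD1 status at entry, nor balances it at allocation, nor uses it in the stated analysis. Patients still accumulating dose and patients no longer accumulating it can both enter and are pooled.

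Two separate things are at stake. The first is the mix at baseline. In a trial of 70, an unbalanced and unadjusted prognostic factor adds variance to the comparison and leaves room for a visible chance imbalance. The second is what happens after randomisation. If neuropathy in one arm is worse and UTD1 is therefore cut more often there, neuropathy in that arm may accumulate more slowly and the arms may move together. Randomisation does not prevent this. A reader shown a small or null difference would need UTD1 exposure by arm to interpret it.

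**Working it through.** **Plan's own figure.** The 35 per arm is given without effect size, SD, power or dropout rate, so it cannot be reproduced. As a reference point only, the standardised difference detectable with 80% power at two-sided 0.05 is (1.960 + 0.842) × √(2/35) = 2.802 × 0.239 = 0.67. So d = 0.67 serves as the yardstick below.

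**Inputs.** From the protocol: 35 per arm, two-sided 0.05, no stratum, unadjusted test. Assumed, because the documents give neither: the share p of entrants continuing UTD1 (0.3 to 0.5), and the difference g in outcome between continuing and stopped patients (0.5 to 1.0 within-group SD).

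**1. Chance imbalance at baseline.** With K of 70 patients continuing UTD1, the number in one arm is hypergeometric (70, K, 35).

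- p = 0.3, K = 21: P(gap of 7 or more patients) = 0.117.
- p = 0.5, K = 35: P(gap of 7 or more patients) = 0.151.

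Seven patients of 35 is 20 percentage points. The chance is about 12% to 15%.

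**2. Precision lost by pooling.** The unadjusted SD is multiplied by √(1 + p(1 − p)g²). Power is Φ(0.67 / (SD × 0.239) − 1.96).

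| p | g | SD multiplier | Power at d = 0.67 | n per arm for 80% |
|---|---|---|---|---|
| none | none | 1.000 | 80% | 35 |
| 0.3 | 0.5 | 1.026 | 78% | 37 |
| 0.3 | 1.0 | 1.100 | 72% | 43 |
| 0.5 | 0.5 | 1.031 | 78% | 38 |
| 0.5 | 1.0 | 1.118 | 71% | 44 |

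The loss is about 2 to 9 points of power. Adjusting for the factor removes this extra variance.

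**3. Size of one imbalance, if it occurs.** A 20-point gap shifts the arm difference by 0.20 × g = 0.10 to 0.20 SD. That is 0.10/0.67 = 15% to 0.20/0.67 = 30% of the yardstick effect. This is conditional on the gap having occurred and is not the trial's error rate.

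**4. UTD1 changes after randomisation.** Dilution = (difference in proportion cut) × (easing after a cut). The documents give neither term. As an illustration, with 30% cut in control, 10% in EA, and an easing of anything from 0 to 15 CIPN20 points, the dilution is (0.30 − 0.10) × 0 to 15 = 0 to 3 points. This shows direction and form only.

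**The case against.** Much of the case on the other side stands.

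- **Baseline mix is noise.** Randomisation balances UTD1 status in expectation, and the chance imbalances in step 1 are already inside the standard error and the 5% error rate. A reader might infer that pooling biases the trial or could manufacture a positive result. The documents do not support that: it would be true of any unstratified prognostic factor, and the significance level covers it.
- **Recovery off UTD1 is not established.** A reader might infer that stopped patients improve within 8 weeks. Relief between courses is stated only for early use, in patients who usually do not want intervention. For later patients the Discussion says the symptoms do not remit between courses, and the Background says that they can last months or years.
- **No ranking of causes.** The text says that severity is closely related to accumulation. It does not say that UTD1 is the largest driver of change over 8 weeks.
- **UTD1 cuts are only possible, and belong to the comparison.** Both passages say may, and no frequency is given. Under intention-to-treat, named in the Abstract, cuts that follow from worse neuropathy are part of the effect of allocation. In the scenario described they pull towards no difference.
- **Avoiding UTD1 reduction is background.** The Objective and Hypotheses concern neuropathy, safety and quality of life, so not naming UTD1 reduction as an outcome contradicts nothing.
- **The article is condensed.** Exposure fields may exist in the case report forms, and covariates may be in an SAP. Table 1 is not a full data inventory.

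What the objection does not remove is that eligibility and allocation are set out in the text shown, and an SAP cannot add stratification after patients are randomised.

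**Conclusion.** The point holds as a worthwhile design improvement, not as a flaw that invalidates the comparison. The protocol identifies UTD1 accumulation as closely tied to severity, yet its entry, allocation and stated analysis make no use of UTD1 status, and its published schedule lists no exposure item.

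The cost at baseline is modest: about 2 to 9 points of power at d = 0.67, and a 12% to 15% chance of a gap of 7 or more patients. Both rest on an assumed 30% to 50% continuing UTD1, and the power loss also on an assumed 0.5 to 1.0 SD difference between the strata. If nearly all entrants continue UTD1, or the strata hardly differ, the cost shrinks towards zero.

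Possible dilution through unequal UTD1 cuts after randomisation is plausible in an open-label trial, but the documents neither show nor size it. The defect there is that readers may be unable to check.

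**What to change.** 1. Determine UTD1 status (further UTD1 planned or stopped) before the envelope is opened. Prepare one envelope set for each status, with permuted blocks of varying size within each set. Two sets filled by simple randomisation would not secure balance.
2. Include that baseline status as a factor in the main comparison.
3. Record from the oncology chart the cumulative UTD1 dose or courses at baseline, and every UTD1 dose, delay, reduction or withdrawal up to week 8.
4. Report these by arm beside the intention-to-treat neuropathy result. Do not adjust the main comparison for UTD1 exposure after randomisation, since that exposure may itself be a result of allocation.

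The cost is a second envelope set and a few chart fields at a single hospital. If allocation is already advanced, items 2 to 4 remain possible, with baseline status taken from the chart. Nothing here asks for any change to UTD1 treatment.

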## Ethics statement

Ethical approval was granted on 26 July 2022 by the Medical Ethical Committee of Cancer Hospital of the University of Chinese Academy of Sciences (Zhejiang Cancer Hospital). The license number is IRB-2022-425. The patients/participants provided their written informed consent to participate in this study.
